## Abstract

**Background:**

A research gap exists for optimal management of cervical radiculopathy in the first 12 weeks and short term natural history of the condition is somewhat unclear, although thought to be favourable. The primary aim of this assessor blinded, superiority, 2 parallel group randomised controlled trial is to investigate the effects of a 4 week physiotherapy programme (6–8 sessions) of manual therapy, exercise and upper limb neural unloading tape, compared to a control of weekly phone advice; on disability, pain and selected biopsychosocial measures, in acute and sub-acute cervical radiculopathy patients. A secondary aim is to identify whether any baseline variables, symptom duration or group allocation can predict outcome.

**Methods:**

Participants are recruited from GP referrals in an urban setting, from a neurosurgery non-urgent waiting list and from self-referral through Facebook advertising. Eligible participants (*n* = 64) are diagnosed with radiculopathy based on a clinical prediction rule and must have symptoms of unilateral, single level, radiculopathy for between 2 and 12 weeks, without having yet received physiotherapy. Random 1:1 group allocation (using variable block sizes), allocation concealment, blinded assessment and intention to treat analysis are being employed. Treatment is provided by clinical specialist physiotherapists in primary and secondary care settings. Outcomes are measured at baseline, 4 (primary endpoint) and 12 weeks. Participants’ report of pain, disability and their rating of recovery is also recorded by telephone interview at 6 months. Statistical analysis of between group differences will be performed with ANOVAs and MANOVAs, and multivariable regression analysis will be undertaken to explore predictor variables. Ethical approval for this study has been received from the Beaumont Hospital and Irish College of General Practitioners Research Ethics Committees. The trial is registered at ClinicalTrials.gov (NCT02449200).

**Discussion:**

An internal pilot study to test retention and recruitment strategies led to trial expansion and this is now a multi centre trial involving 5 clinical sites.

**Trial registration:**

NCT02449200. Registered 20/05/15.

## Background

Cervical radiculopathy (CR) has been defined by the North American Spine Society (NASS) as pain in a radicular pattern in one or both upper extremities related to compression and/or irritation of one or more cervical nerve roots, with signs and symptoms including varying degrees of sensory, motor, and reflex changes in addition to dysaesthesia and paraesthesia [1]. People with CR often experience high levels of pain and disability [2] and present to primary carers seeking diagnosis, reassurance and treatment, for a condition thought to have a favourable natural history of recovery over weeks and months [3, 4]. Ten years have passed since the Taskforce on Neck Pain highlighted the existence of a research gap for its optimal management [5], during the World Health Organisation’s (WHO) Bone and Joint Decade (2000–10); and although several clinical guidelines now exist for CR management [1, 3, 6, 7], they often rely heavily on consensus and have universally highlighted the paucity of high quality, randomised controlled trials.

The lack of quality trials is most evident in recent onset (12 weeks) CR, making evidence-based clinical decision-making a challenge for primary carers. Danish clinical guidelines recommend monitoring the individual patient’s clinical course to guide treatment decisions during this timeframe [6]. With a prevalence less than half that seen for lumbar radiculopathy [8], trial recruitment for recent onset (less than 3 months) CR is challenging.

Conservative treatment approaches described to date, have included pharmacology, advice to remain active, manual therapy, exercise, acupuncture, traction, collars and epidural injection [5, 6]. Manual therapy can include muscle energy techniques, high velocity manipulation or low velocity mobilisation of the cervical and/or thoracic spine, soft-tissue mobilisation and neural mobilisation techniques [9, 10]. Exercise in cohort studies and clinical trials has included mobility exercises, deep neck flexor and/or shoulder muscle endurance and strengthening [11, 12].

Not surprisingly, given the small evidence base for conservative management of CR, little is known about predictors of good clinical outcome. Cleland et al. [11] identified a four-variable model that detected participants who were most likely to demonstrate short-term, i.e. after 1 month, improvement with conservative treatment. This model included participants who were older than 54 years, whose dominant arm was not affected, whose symptoms were not aggravated by cervical flexion and who received multi-modal physiotherapy made up of manual therapy, cervical traction and deep neck flexor strengthening for at least half of their visits to the clinic. When all four variables were present, the positive likelihood ratio was 8.3 (95% CI = 1.9–63.9) [11].

The PACeR trial protocol is registered at ClinicalTrials.gov (NCT02449200) and is investigating the effectiveness of multimodal physiotherapy in comparison to an advice control, in recent onset CR.

### Aims

The trial’s primary aim is to investigate the effects of a multimodal physiotherapy (MP) programme on the independent primary outcome measures of disability, using the Neck Disability Index [13]; and pain, using the NPRS for both neck and arm pain at 4 weeks [14].

Secondary aims are;

To investigate the effects of the MP programme on selected biopsychosocial outcome measures at 4 and 12 weeks;I.Patient reported outcome measures -◦ Health-related quality of life using the SF-12 version 2 Health Survey [15].◦ Mood using the Hospital Anxiety Depression Scale (HADS) [16].◦ Fear avoidance using the Fear Avoidance Belief Questionnaire (FABQ) Neck [17, 18]. ◦ Patient rating of recovery using the Global Rating of Change scale [19].II.Clinical physical examination measures -◦ Cervical range of motion measured with a CROM 3 device (Performance Attainment Associates, USA). Flexion, extension, bilateral side flexion and rotation are being measured.◦ Pressure pain threshold (PPT) measured with pressure algometry [20], and the Upper Limb Neurodynamic Test (ULNT) 1 [21, 22] as measures of nerve mechanosensitivity.To identify whether any of the biopsychosocial outcome measures, as well as PainDETECT [23] at baseline, symptom duration and group allocation; can predict outcome (pain and disability) at 3 months.

### Hypothesis

A 4 week multimodal physiotherapy programme will lead to changes in self-reported disability and pain, compared to only advice to stay active, in patients with recent onset CR. The null hypothesis is that there will be no difference in pain and disability between the intervention group receiving a multimodal physiotherapy programme, and the control group receiving advice. Both groups can also continue to use medication throughout the trial, as prescribed by their GP.

## Methods

### Study design

The PACeR trial is an exploratory, two parallel group, assessor-blinded, multi-centre randomised controlled trial, with a primary endpoint of pain and disability at 4 weeks. This is a superiority trial to investigate a novel, complex physiotherapy intervention using allocation concealment, blocked randomisation and a 1:1 allocation ratio. The SPIRIT statement and CONSORT guidelines are guiding the reporting and conduct of the study [24, 25]. Ethical approval for this study has been granted by the medical research ethics committees of Beaumont Hospital (REC ref. 14/85), the Irish College of General Practitioners (ICGP) and the Royal College of Surgeons in Ireland (RCSI). Recruitment is via GP referral, self-referral through social media advertising, and initially, also from a waiting list of non-urgent referrals to a national neurosurgery centre. Five clinical centres (1 hospital and 4 private practices) are currently providing the trial’s interventions. Physiotherapy is provided by postgraduate master’s level or clinical specialist musculoskeletal physiotherapists.

### Eligibility criteria

Adults with single-level cervical radiculopathy of less than 12 weeks duration are eligible to participate. Inclusion & exclusion criteria are adapted from studies of similar cohorts [26, 27].

Inclusion criteria:Participants aged 18 years or older.Meet criteria for CR diagnosis on a clinical prediction rule (CPR) by demonstrating positive responses to at least 3 of the following clinical tests: Spurling’s Test, Upper Limb Neural Tissue Provocation Test 1 (ULNT 1), Cervical Distraction Test, and cervical rotation (less than 60°) on the symptomatic side [28].Complains of neck or periscapular pain in addition to radicular pain, paraesthesia or numbness in the upper limb; aggravated by neck posture or movement [29].Symptom duration must be greater than 2 weeks and less than 3 months.Mean of Numerical Pain Rating Scale (NPRS) scores for both neck and arm pain must be ≥3/10.Fluent in spoken & written English.

Exclusion criteria:Previous physiotherapy or manual treatment to cervical spine within past 6 months.Previous epidural injection since the onset of current symptoms.Prior surgery to the cervicothoracic spine or currently symptomatic upper limb.Current bilateral upper-limb symptoms.Myotomal paresis less than 4/5 on Medical Research Council (MRC) Scale in affected upper limb.Signs and symptoms suggestive of Cervical Spondylotic Myelopathy (CSM): bilateral paraesthesia, hyperreflexia, positive Babinski reflex and spasticity.Diagnosis of any generalised neurological disorder e.g. multiple sclerosis.Concurrent peripheral neuropathy affecting either upper limb e.g. carpal tunnel syndrome, thoracic outlet syndrome.Medical red flags suggestive of serious pathology such as neoplastic conditions, upper cervical ligamentous instability, vertebral artery insufficiency and inflammatory orsystemic disease [30].Diagnosis of fibromyalgia.Psychiatric diagnosis in past 6 months.Ongoing litigation relating to cervical symptoms.

A two-step screening process is used to determine eligibility. A successful phone screen is followed by physical examination. Physical exam includes a neurological exam and manual exam of the cervical spine (C2-T2) to identify the symptomatic nerve root level.

If an MRI of the patient’s cervical spine has been undertaken, the report is reviewed for concordance after the initial assessment.

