### Randomisation

The allocation sequence has been generated by an independent academic colleague using a computer-generated list of random numbers and randomly varied block sizes of 4 and 6 from www.randomization.com. The allocation sequence is concealed from the PI, who enrols and consents participants. The PI informs the randomiser when a new participant has been enrolled and once randomised, the randomiser directly informs the relevant physiotherapist, who informs the participant of their group allocation by phone. Participants are randomly assigned using a 1:1 group allocation ratio. The PI is blinded to group allocation until the 12 week assessment. Given the nature of the interventions, it is not possible to blind the participants or therapists involved in providing either intervention.

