### Data analysis plan

Baseline demographic characteristics and all outcome measures will be described and analysed using SPSS (IBM, version 24) or Stata statistical software (Statacorp LLC, Release 15). Descriptive characteristics will be presented for both groups following the CONSORT Statement. Data will be checked for normality using the Shapiro-Wilk test. Marginal effects will be used to calculate effect sizes for specified values for baseline differences. Results will be reported as mean differences between the groups and their 95% confidence intervals. Poisson regression will be used where data are non-parametric (Bland and Altman, 2011).

Statistical analysis will include two-way (treatment x time) ANOVAs and MANOVAs for between and within-group differences and interactions. Intention to treat analysis will be the primary approach employed. A per protocol analysis will also be undertaken and results compared to assess the impact of data that is not missing at random (NMAR) (Armijo-Olivo et al., 2009).

Secondary analysis will explore if any of the baseline outcome measures, symptom duration and group allocation are predictors of outcome (pain and disability) at 3 months. Appropriate multivariable regression analysis will be performed (linear or logistic).

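### The 4-week comparison names no baseline covariate, leaving symptom duration out and the choice of adjustment open

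*Protocol article*

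**What the plan says.** All places are in the protocol article.

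- **Eligibility criteria:** "Symptom duration must be greater than 2 weeks and less than 3 months".
- **Background:** cervical radiculopathy is described as "a condition thought to have a favourable natural history of recovery over weeks and months". The Abstract is more cautious: "short term natural history of the condition is somewhat unclear, although thought to be favourable".
- **Study design:** the trial runs "with a primary endpoint of pain and disability at 4 weeks".
- **Randomisation:** 1:1 with "randomly varied block sizes of 4 and 6". No stratification factor is named.
- **Data analysis plan, group comparison:** treatment-by-time ANOVAs and MANOVAs, with no covariate named. On adjustment it says only: "Marginal effects will be used to calculate effect sizes for specified values for baseline differences".
- **Data analysis plan, secondary analysis:** a regression to explore whether baseline outcome measures, "symptom duration and group allocation are predictors of outcome (pain and disability) at 3 months". The Aims section gives symptom duration the same role. The article gives it no other analytic use.

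**The concern.** The entry window of about 10 weeks is longer than the 4 weeks to the primary endpoint, and it lies on the same timescale as the expected recovery. If time since onset influences how much a person improves over the next 4 weeks, that variation stays in the residual of a comparison that ignores it. The protocol considers duration plausible enough as a predictor to test it, but places it in a different analysis at a different time point.

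The adjustment sentence adds a second difficulty. It implies some baseline-adjusted model without saying which variables enter. One natural reading is that they are picked according to the differences observed between the arms. The reported estimate would then depend on a choice made after seeing the data.

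At stake are some precision, which is scarce with 64 participants, and the credibility of the adjusted result.

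**Working it through.** **The plan's own figures.** Inputs from Sample size estimation: NDI difference 7, SD 9.2; NPRS difference 2, SD 1.85; two-sided 5%, power 80%. The normal approximation for NDI is 2 × (9.2 × (1.960 + 0.842) / 7)² = 27.1, so 28 per arm. With the t distribution the answer is 29 per arm (power 81.3%). For NPRS the two methods give 14 and 15. The stated 29 and 15 are reproduced. The total follows as 58 × 1.10 = 63.8, so 64.

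**Chance imbalance in duration.** Assume entry is uniform over 2 to 12 weeks (the article gives no distribution).

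- SD of duration = 10/√12 = 2.89 weeks.
- SE of the between-arm difference in mean duration at 29 per arm = 2.89 × √(2/29) = 0.76 weeks; 95% range ±1.5 weeks.
- A gap above 1 week has probability of about 19%. With an SD of 2.0 or 3.5 weeks instead, it is 6% or 28%.

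**Effect on the NDI comparison.** The total SE of the unadjusted 4-week difference is 9.2 × √(2/29) = 2.42 points, a 95% range of ±4.7. Let r be the correlation of duration with 4-week NDI, which is an assumption throughout. The part of that range due to duration is 1.96 × r × 2.42. The share of variance is r². After adjustment the residual SD is 9.2 × √(1 − r²). The implied slope is r × 9.2/2.89 points per week.

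| Assumed r | Slope (NDI points per week) | Shift from duration imbalance (95% range) | Variance explained | Power at 29 per arm after adjustment |
|---|---|---|---|---|
| 0.1 | 0.32 | ±0.5 | 1% | 81.6% |
| 0.3 | 0.96 | ±1.4 | 9% | 84.7% |
| 0.5 | 1.59 | ±2.4 | 25% | 90.8% |

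The power column uses the t distribution, compares with 81.3% unadjusted, and ignores the degree of freedom spent. The shifts are 95% ranges, not maxima, and lie within the ±4.7 rather than adding to it.

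**Plausibility of the upper row.** Over the 10-week window, slopes of 0.32, 0.96 and 1.59 imply differences of 3.2, 9.6 and 15.9 NDI points between the earliest and latest entrants. The last is more than twice the 7-point MCID, so r = 0.5 is a strong assumption.

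**Type I error.** In 40,000 simulated trials with 29 per arm, the unadjusted t-test rejected a true null in 4.9% of trials at r = 0.3 and 5.1% at r = 0.5. Among trials with a duration gap above 1 week the figures were 7.4% and 12.1%. The test is therefore valid overall, and its error rate is raised only conditionally on an imbalance.

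**Limits.** These figures treat duration alone. Baseline NDI is likely to explain part of the same variance, so the gain from duration beyond baseline score is probably smaller; nothing in the article allows it to be estimated.

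**The case against.** The strongest reply has four parts.

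1. **Chance imbalance is ordinary sampling variation.** With concealed 1:1 allocation the unadjusted estimate is unbiased in expectation and its standard error already covers imbalance in duration. This stands in full.
2. **Nothing in the article shows that duration is prognostic.** It is one of many candidate predictors, and the Abstract calls the short-term course somewhat unclear. This also stands, and it is why the size can only be given as a range.
3. **Adjustment is partly there already.** The marginal-effects sentence implies a baseline-adjusted model, and the 3-month regression may hold duration and group together. This stands in part. It would be wrong to say that the plan does not adjust at all. But the sentence names no variable, and the 3-month regression is not the primary 4-week comparison.
4. **A condensed article may leave the covariate list to an analysis plan that is not shown.** A bare omission would indeed be no finding. Here, however, the article states its group comparison, states an adjustment approach in loose terms, and assigns duration to another analysis. The point concerns those stated choices.

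**Conclusion.** The point holds as a low-cost improvement in precision and prespecification. The stated 4-week model names no baseline covariate, the adjustment wording leaves the variables open, and a variable that the protocol regards as a possible predictor is kept for the 3-month regression.

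The gain cannot be sized from the documents. For assumed correlations of 0.1, 0.3 and 0.5, duration explains 1%, 9% and 25% of the variance in 4-week NDI, and probably less beyond baseline score. At the low end the gain in power is negligible, and the main benefit is that the covariates are settled in advance.

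A reader might infer that differences in natural recovery bias the treatment effect, that the 2-to-12-week window is an error, or that allocation had to be stratified by duration. The documents support none of these. Randomisation protects the estimate and the overall 5% error rate, no passage contradicts the window, and leaving a trial of 64 unstratified by duration is a normal choice. A data-driven selection of covariates is likewise only one reading of an ambiguous sentence, not something that the plan declares.

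**What to change.** For NDI and NPRS at 4 weeks, and likewise at 12 weeks, specify a between-group model with two fixed covariates: the outcome's own baseline value and symptom duration at baseline in weeks, entered as a continuous variable. State that this set replaces adjustment for baseline differences and will not be changed in the light of observed imbalance. Any marginal effects should be computed from this model.

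The change takes a sentence or two in the Data analysis plan. Both baseline scores are already collected, and duration has to be established for eligibility and for the predictor aim. Each covariate costs about one degree of freedom, and no larger sample is needed. If duration proves weakly prognostic, little precision is gained from it. The eligibility window and the randomisation need no change.

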### Interventions

All participants are advised on CR’s natural history, positions of ease, to stay active and to take prescribed medication as appropriate.

Participants allocated to the MP group receive 4 weeks (6–8 sessions) of non-provocative manual therapy, exercise and upper limb neural unloading tape (Fig. 1), as decided by the treating physiotherapist from a best-practice physiotherapy treatment manual. Previous RCTs investigating physiotherapy for nerve-related arm pain or cervical radiculopathy have involved 2 to 6 week programmes [27, 31, 32]. All participants receive lateral glide mobilisation [33] to the appropriate segmental level, applied using a treatment algorithm modified from Nee et al. [26]. Treating therapists are also permitted to use passive accessory or intervertebral mobilisations at this level, if the lateral glide does not yield clinical benefit. Additional joint mobilisations [34] to segmental levels above or below (C2 to T4) can also be applied, as deemed necessary by the treating physiotherapist e.g. to address segmental hypomobility.

**Fig. 1 Fig1:**
[figure not shown]
Neural unloading tape. Hypoallergenic Fixomull applied first as underwrap (left) with zinc oxide applied with tension, with arm supported below the elbow (right)

All participants also receive exercise, including deep neck flexor (DNF) strengthening, mobility exercises and scapular muscle endurance exercise. The primary rationale for including exercise in this complex intervention is to achieve pain relief. Peripheral neuropathic pain and nociceptive pain mechanisms are known to co-exist in radiculopathy [35] and as such, it is to be expected that various exercises may be of benefit. Low level evidence already exists to support a variety of exercise types such as neck ROM, DNF training and scapular training, but primarily in the production of only short-term pain relief and to a lesser extent, functional improvement [31, 36], after 4 to 6 weeks of exercise. Given the painful and disabling nature of this condition, pain reduction even in the short-term is likely to be of value to the individual patient with CR. However, medium to long term improvement in pain and function, leading to improved social participation, should be a secondary focus of any exercise intervention in this cohort. A clear understanding of axioscapular muscle dysfunction has not yet been achieved for CR and so a pragmatic approach to exercise prescription has been adopted in this trial, with the intention of providing a bespoke programme to address actual deficits identified. Non-provocative, progressive endurance and strengthening for muscles of the neck and scapular region are also embedded into the programme and prescribed at the therapist’s discretion. As this intervention is of only 4 weeks’ duration, participants are advised to continue appropriate exercises until their 12 week assessment.

The third element to this complex intervention is upper limb neural unloading tape, adapted from McConnell [37]. Tape is applied in order to offset the upper limb load and provide relief of arm pain. Hypoallergenic 5 cm wide Fixomull and 3.8 cm zinc oxide tape is applied for 24–48 h. Treating therapists received 2-h training and agreed to follow the assessment and training manual. Recording of treatment sessions was done using standardised report forms.

Control group participants are phoned by a physiotherapist on a weekly basis for 4 weeks. They provide an update on their symptom profile and receive advice.

All participants are asked to forego any other physiotherapy external to the trial prior to the 12 week time point. To optimise retention, control group participants are offered treatment at 12 weeks.

